### Handling Missing Data

Our general approach to missing data involves using all observed information while not exaggerating the precision of findings based on incomplete data [57,58]. All variables described for our final regression models will be used in our imputation procedures, that is, outcome measures, intervention condition, baseline outcome variables, strata variables (sex and race), age, and health system. The study group participant data will be imputed separately [59]. Multivariate imputation by chained equations methods using PROC MI and MIANALYZE procedures in SAS (SAS Institute) will be used to create multiple imputations for multivariate missing data (eg, continuous, binary, unordered categorical, and ordered categorical data) based on a fully conditional specification, where each incomplete variable is imputed by a separate model [60]. All missingness (nonresponse, attrition, or loss to follow-up) will be treated the same way for our benchmark analysis. Sensitivity analyses will be explored where reasons for attrition are accounted for in the generation of imputed covariate and outcome values. All variables (ie, outcome and baseline characteristics) described in the aforementioned models will be used for imputation procedures. The number of datasets to be imputed will be determined using the quadratic rule [61].

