## Methods

### Study Design

This study is a randomized controlled trial of 160 ADRD care partners to evaluate the real-world efficacy of Brain CareNotes on the primary outcomes of care partner burden and patients’ BPSD; patients with ADRD are not enrolled in the study, only their care partners are enrolled. Participants will be recruited from 2 health systems, by word of mouth, and from community outreach efforts and randomized to receive either the Brain CareNotes intervention or an education-only attention control app. Participants will remain in the study for 12 months.

The primary objectives of this trial are to test the effect of Brain CareNotes on (1) care partner burden and (2) patients’ BPSD after 12 months of use. Both primary outcomes will be assessed using the care partner-reported Neuropsychiatric Inventory (NPI) [32,33].

The secondary objectives are to test the effect of Brain CareNotes on (1) care partner depressive symptoms and (2) patient and care partner acute care use at 12 months. For care partner depressive symptoms, we will use the researcher-administered 9-item Patient Health Questionnaire-9 [34,35]. Acute care use data will be obtained from participant self-reports to identify both their and the patients’ hospital and emergency room visits that occurred within 12 months of enrollment.

To measure the predicted social-behavioral mechanisms mediating the efficacy of Brain CareNotes, we will also measure (1) care partner self-efficacy and (2) care partner social support at baseline, 6 months, and 12 months. These are measured using the Revised Scale for Caregiving Self-Efficacy [36] and the Multidimensional Scale of Perceived Social Support (MSPSS) [37], respectively.

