### Setting and Participants

This study has a planned enrollment of 160 care partners of patients with ADRD. There will be 80 participants in the intervention arm and 80 in the attention control comparator. We will obtain lists of eligible care partners’ contact information from partner health systems in Indiana, United States, including (1) primary care clinics at Indiana University Health (a nonprofit academic health care system), (2) Healthy Aging Transition Services clinics at Community Health Network (a nonprofit health care system), and (3) Eskenazi Health (a public health care system with special emphasis on vulnerable populations in Indiana). Care partners will be identified either by searching patient databases for patients with an ADRD diagnosis (the care partner will be their contact person) or by working with health care professionals at specific clinics to identify potentially eligible care partners. We will also distribute study information at conferences, in communities of interest, and by word of mouth (Multimedia Appendix 1). In addition to these recruitment efforts, our study is listed in databases such as ClinicalTrials.gov and Indiana University’s All IN for Health study listings. These postings reach potential participants statewide, nationwide, and internationally. We will consider international participants on a case-by-case basis and take into account international research ethical standards.

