### Randomization

We will use a permuted block randomization scheme implemented within REDCap. Randomization will be stratified by recruitment source. Participants will be randomized after the baseline assessment by unmasked research staff. Research personnel masked to the randomization of individual participants will perform all primary and secondary data collection at the 6- and 12-month follow-ups. Participants will not be informed which app is the intervention and which is the control.

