### Analyses

At 12 months, the NPI Caregiver Distress scale will be compared between study groups using an analysis of covariance model with fixed effects for Brain CareNotes (vs attention control), health system, age, sex, race, recruitment source, and baseline values for NPI Caregiver Distress and NPI Total Score scales. For between-group comparisons, the difference in least squares means, corresponding SE, 2-sided 95% CIs, and 2-tailed *P* value will be derived from this analysis of covariance model and presented. Within-group change (least squares) means, corresponding SEs, 2-sided 95% CIs, and 2-tailed *P* values will also be presented. Standard model diagnostics will be performed to assess the validity of the proposed model; these diagnostics will include an examination of the residuals for normality, linearity, and homoscedasticity as well as testing for the significance of the intervention by baseline values interaction term to examine if intervention effect differs depending on the baseline levels of NPI Caregiver Distress or NPI Total Score scales.

The NPI Caregiver Distress scale will also be analyzed using a generalized linear mixed model (GLMM) [54,55] with an identity link function. GLMM allows us to analyze longitudinal data at each time point (baseline, 6 months, and 12 months) adjusting for multilevel dependencies within an individual (nested in the study group) and to explore additional covariates as mentioned earlier. Random intercepts, slopes, and fixed covariate effects will be estimated as needed. Time will be modeled as a continuous and categorical variable to model linear and nonlinear changes in care partner burden, respectively. The interaction between study group and time (ie, days between assessments) will be tested to determine if the rate of change in care partner burden is different between study groups. Standard model diagnostics will be performed to assess the validity of proposed models; these diagnostics will include examining the residuals for normality, linearity, and homoscedasticity and testing for the significance interaction term of the intervention by the baseline levels of the NPI Caregiver Distress and NPI Total Score scales. The variance-covariance structure of the random effects will be dependent on the variability among participants within groups. A preliminary test will be conducted to assess the significance of the homogeneity of variances [56] for within-group differences.

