Analysis for patients’ BPSD and care partner depressive symptoms will be the same as for care partner burden, using the NPI Total Score scale and PHQ-9, respectively.

Acute care use will be analyzed as a dichotomous outcome (ie, yes or no for at least 1 emergency department or hospital visit—cumulative incidence) using a generalized linear model, specifically, a log-binomial regression model with fixed effects for Brain CareNotes (vs attention control), strata, and covariates described earlier. For the between–study group comparison, the estimated risk ratio (relative risk), SE, 95% Wald CI, and *P* value will be presented. Standard model diagnostics to assess final model validity and assumptions will be implemented.

As in the primary analysis, we will use a GLMM [54,55] with a log link function to model cumulative incidence. In addition, a Poisson model (GLMM with log link function and offset variable for follow-up duration) will be examined to model the incidence rate of acute care visit counts during the 12-month follow-up period.

The potential for 3-way and 2-way interactions will be examined to identify participant characteristics associated with increased benefit of the intervention. If statistically significant interactions are observed, additional intervention effect results will be presented as subgroup analyses to highlight intervention effect modifiers on primary and secondary outcomes separately.

Measures related to improved psychosocial outcomes (ie, social support and self-efficacy) will be tested as a potential mediator or moderators of intervention effects. We will also examine baseline characteristics (eg, sex and age) related to psychosocial outcomes as potential intervention effect moderators.

Similarly, mechanism measures (MSPSS and Revised Scale for Caregiving Self-Efficacy) will be evaluated for their potential mediation effect on the primary and secondary outcomes. We will also use investigate patient characteristics (FAQ or QDRS) as potential moderator. All analyses related to study primary, secondary, and mechanism outcomes will be performed by researchers masked to treatment condition.

Linear regression and classification and regression trees will be used to examine the effect of intervention timing, participant ratings on usability, acceptance, and actual use of technology on intervention efficacy.

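### The stratification factor is named two ways, the explicit imputation list leaves out the one used for randomization, and the overlapping health-system and recruitment-source terms have no defined levels

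*Protocol article*

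**What the plan says.** All references are to the protocol article.

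- **Randomization:** "Randomization will be stratified by recruitment source". No other factor is named.
- **Analyses, primary ANCOVA:** besides treatment, the fixed effects are "health system, age, sex, race, recruitment source, and baseline values for NPI Caregiver Distress and NPI Total Score scales". Sex and race are ordinary covariates here. Health system and recruitment source are two separate terms. Both a between-group difference and within-group change least squares means are promised.
- **Analyses, acute care use:** "specifically, a log-binomial regression model with fixed effects for Brain CareNotes (vs attention control), strata, and covariates described earlier". The word strata is not defined there.
- **Handling Missing Data:** the rule is "All variables described for our final regression models will be used in our imputation procedures, that is, outcome measures, intervention condition", and the list then continues with "baseline outcome variables, strata variables (sex and race), age, and health system". Recruitment source is not on it. A later sentence in the same section says again that all outcome and baseline variables of the models enter the imputation.
- **Study Design:** "Participants will be recruited from 2 health systems, by word of mouth, and from community outreach efforts".
- **Setting and Participants:** three partner health systems are listed, together with word of mouth, community distribution and study listings that reach people outside the state and the country.

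**The concern.** Two sections name different stratification factors, and both cannot describe this trial. An analyst has to know which variable was used to randomize, because the analysis is meant to adjust for it and the log-binomial model calls for it by the name strata.

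The same sentence governs the imputation. An imputation model that lacks a term of the analysis model is uncongenial with it: the imputed values carry no association between the outcome and the omitted factor beyond what the other variables convey, so that coefficient is pulled toward zero and the combined standard errors need not be right.

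The third issue is overlap. The recruitment sources are described as the health systems themselves plus routes outside them, so health system and recruitment source share content. If one determines the other, the model contains redundant columns, and some of the promised summaries may have no unique value.

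**Working it through.** There is no stated figure to reproduce. The check is a comparison of sections, followed by a design-matrix check under assumed codings.

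**1. Which variables are the strata?** Randomization: recruitment source. Handling Missing Data: sex and race. No section says that randomization used sex or race. The two statements conflict.

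**2. Is the imputation list complete?**

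| ANCOVA term (Analyses) | On the explicit imputation list? |
|---|---|
| Treatment | yes |
| Baseline NPI scores | yes |
| Age, sex, race | yes |
| Health system | yes |
| Recruitment source | **no** |

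The list is introduced as equivalent to all final-model variables, so it breaks its own rule by one term, and that term is the randomization factor.

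**3. How much imputation is at stake?** The Sample Size section plans for N = 160 and 75% retention: 160 × (1 − 0.75) = 40 twelve-month outcomes.

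**4. Do health system and recruitment source alias?** The article does not define their levels, so I assumed some: three systems, word of mouth and outreach, for 160 simulated participants. Columns are the intercept plus (levels − 1) for each factor. Health system has 4 levels in every coding.

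| Coding (assumed) | Columns | Rank | Equal-weight LS mean estimable? | Treatment difference estimable? |
|---|---|---|---|---|
| A. Source names each system; health system is *none* for other recruits | 1+4+3 = 8 | 5 | no | yes |
| B. Source is system / word of mouth / outreach; health system is *none* for other recruits | 1+2+3 = 6 | 5 | no | yes |
| C. Source as in B; health system is place of care, recorded for everyone | 6 | 6 | yes | yes |
| D. Source as in A; health system as in C | 8 | 8 | yes | yes |
| E. Both terms have the same four levels | 1+3+3 = 7 | 4 | yes | yes |

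Adding treatment adds one column and one rank to each row (B becomes 7 columns, rank 6; E becomes 8 columns, rank 5). Estimability was tested with L(X′X)⁻X′X = L.

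The reason A and B fail is simple. In A, weighting the five sources equally puts 2/5 on health system *none*, whereas weighting the four health-system levels equally puts 1/4 on it. In B the figures are 2/3 and 1/4. The two sets of weights cannot both hold. In E they coincide. With observed-margin weights, the means are estimable in all five codings.

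**5. What does the imputation lose if the list is followed?** Source information not already carried by health system is rank(both) − rank(health system alone), where the latter is 4: A, 5 − 4 = 1; B, 5 − 4 = 1; C, 6 − 4 = 2; D, 8 − 4 = 4; E, 4 − 4 = 0. The omission therefore matters most where the two terms overlap least.

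**6. How many systems?** Study Design says two; Setting and Participants lists three. The systems form part of the recruitment source, so the count bears on its levels.

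**The case against.** The strongest reply is that Handling Missing Data does not decide to exclude recruitment source. Its opening rule and a later sentence both take in every model variable, and recruitment source is one. That stands: the fault is an incomplete list between two inclusive rules, not a settled exclusion. It remains a fault, because a programmer working from the explicit list would leave the factor out.

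On the overlap, a reader might infer that the ANCOVA is rank-deficient and its least squares means not estimable. The article does not support that as fact. It gives no levels, and coding of levels is commonly left to fuller documents. Eligible patients must be receiving primary care, so health system may well mean place of care, and then the model has full rank. Even with identical levels the equal-weight means are estimable.

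A reader might also infer that people recruited outside the partner systems would drop out of the model or have a health system imputed for them. That needs a blank field, which nothing in the article indicates; a *none* category would avoid it. The article also gives no share of such recruits, so no count can be attached.

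Finally, the undefined strata in the acute-care model has little numerical consequence. Sex, race and recruitment source are all among the earlier covariates, so either reading yields the same terms.

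**Conclusion.** The contradiction over the stratification factor, and the omission of recruitment source from the explicit imputation list, are wrong as written and rest on no assumption. If the list is followed, the imputation model is uncongenial with the primary analysis for about 40 of 160 outcomes at planned retention. The information lost ranges from nothing to four columns, depending on coding, and no effect on an estimate has been calculated.

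The overlap of health system and recruitment source is real in the description, but its degree is unknown. Under partial nesting (codings A and B) it makes equal-weight within-group least squares means non-estimable. The article does not say which weights will be used. The treatment difference is estimable under every coding checked, and nothing here changes the sample size or alpha. This is a correction that should be made, of modest likely size.

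**What to change.** 1. In Handling Missing Data, replace the strata wording in "strata variables (sex and race), age, and health system" with *stratification variable (recruitment source), sex, race*, keeping age and health system. This puts recruitment source in the imputation model and removes the conflict with Randomization.
2. In the acute-care model, state that strata means recruitment source.
3. Define the levels of recruitment source and of health system as coded in REDCap, including how health system is recorded for people recruited outside the partner systems. Merge the two into one factor only if one determines the other. If health system records place of care for everyone, it is a legitimate separate covariate and should stay.
4. Reconcile the two health systems in Study Design with the three in Setting and Participants.

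The cost is wording in four sections (Study Design or Setting and Participants, Randomization or its cross-reference, Analyses, Handling Missing Data). No new data are needed. The article says analysis starts only after the last participant finishes, estimated for spring 2026, so the correction should be dated before then.

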### Data and Safety Monitoring Plan and Board

The principal investigators (PIs), along with the independent data and safety monitoring board (DSMB), will be responsible for data and safety monitoring during the duration of the study. PIs will work to ensure the daily safety of participants, while the DSMB will advise PIs and National Institute on Aging program staff on the safety of participants, potential study risk and benefits, the ethicality of the study, scientific integrity, and participant recruitment.

The study team will meet with PIs on average at least every 2 weeks to discuss the ongoing progress of the study, data collection, and participant safety. Any reportable events will be discussed and reported within 48 hours (about 2 days). PIs will work will research staff to submit a written report to the DSMB every 6 months, unless otherwise recommended by the DSMB. This report will include study updates on the following: participant recruitment, accrual, randomization, and retention; treatment delivery and fidelity; data collection and quality; any adverse events that have occurred; and any protocol deviations that have occurred.

All participant data will be compiled and stored in the study’s HIPAA-compliant REDCap databases. Participant contact information will be collected from partner health system’s electronic databases and manually entered by the data management team. Participants’ survey responses, acute care use, and adverse events will be collected during assessment administration and entered directly into the database. App use will be estimated via app server queries that will be stored in IRB-approved databases. All data will be routinely reviewed for errors and cleaned by the data management team.

## Results

From May 2023 to March 2025, we have enrolled 159 participants, and 42 have successfully completed the study. Data analysis will begin once the final participant has completed their involvement in the study (estimated in spring 2026), and we anticipate results of these analyses will be published in late 2026 or early 2027. Results will be available to participants and the public on the study’s ClinicalTrials.gov (NCT05733520) page, and participants will be reminded of that link 1 month before their completion of the study.

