**Figure 2 figure2:**
[figure not shown]
Brain CareNotes features.

Brain CareNotes mobile telehealth app features.Care skill support features: users have 24/7 access to written and visual materials on developing care skills. These materials cover a range of topics, including (1) care partner burden, (2) understanding the patient with memory loss, (3) exercise, (4) personal care, (5) behaviors, (6) safety, and (7) delirium.Care coach support: each care partner user is assigned to a personal care coach employed by the study team. Care coaches operate remotely using a mobile phone or computer-based secure and HIPAA (Health Insurance Portability and Accountability Act)–compliant portal. Care coaches perform the following tasks daily: (1) monitor, respond to, and initiate messages to and from Brain CareNotes users; (2) address user activity, including new assessments; and (3) schedule and conduct biweekly or monthly phone calls with the care partner.Assessments and tracking: every 2 weeks, users are prompted to self-administer the Healthy Aging Brain Care Monitor [45,46]. Once an assessment is completed, results are immediately displayed in easy-to-read, color-coded visualizations with interpretation of whether scores are normal, mild, moderate, or severe. Past measurements can be displayed on demand to compare recent scores and assess change over time. Care coaches receive daily notifications when an assessment was completed or a message was received from a care partner.Responding to change over time: Brain CareNotes has bidirectional secure messaging, allowing unpaid care partner users to communicate back and forth with the care coach or for the care coach to initiate a conversation. Moreover, when a care partner reports a patient or care partner symptom, the app generates a set of specific CareNotes associated with each reported symptom.

Participants randomized to receive Brain CareNotes will be sent a HIPAA (Health Insurance Portability and Accountability Act)–compliant link to create an app account on their personal device. This researcher-generated link is required to gain access to Brain CareNotes. If the participant does not have a mobile device meeting the minimum technical requirements, a smartphone with an unlimited network data plan from AT&T, along with unlimited text messaging and pooled voice minutes, will be provided for the duration of the study.

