### Description of the Attention Control App

Participants randomized to the attention control group will receive the Dementia Guide Expert app, an existing BPSD mobile app freely available in the Google and Apple app stores. It was developed by the ENGAGE-IL initiative at the University of Illinois at Chicago (Health Resources and Services Administration grant U1QHP28730). Dementia Guide Expert provides education only, with no interactive BPSD management support, coaching, assessment, or external response. It contains “evidence-based expert information on what dementia is, types, contributing factors, risks, symptoms, stages, diagnosis, tests, treatment, management, communication techniques, and links to resources and support services” [47]. We will use an attention control comparator to mimic the intervention group’s use and access to technology, frequency and type of contact with research staff (ie, for installation and technical support), and expectancy of benefit [48].

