### Limitations and Potential Challenges

There are some limitations and potential challenges to this study. First, while we have had success in recruiting participants on time, there are concerns about retaining participants in the study for the entire 12-month duration. Sample size was calculated assuming a 75% participant retention rate, as the 6-month pilot had 85% of participants complete the study. However, the likelihood of care recipient death or nursing home placement increases with the duration of the study, and this may impact our ability to retain as many participants as previously anticipated. In addition, our team does not have the ability to control the “dosing” of the intervention that participants receive, as they are able to use Brain CareNotes at their own discretion. This means that those randomized to the intervention group likely have differing app use patterns, which could affect its efficacy. While this is reflective of real-world use patterns of commercially available mobile apps, we are attempting to control this by sending app use reminders to participants in both the intervention and control groups every 2 weeks. Currently, Brain CareNotes is a website optimized for mobile viewing, so it is compatible with all mobile devices that can access the internet through a browser. In the future, it could be adapted into an app and made widely available on public app marketplaces (eg, Apple App Store and Google Play Store) for download onto a mobile device. While there are costs associated with Brain CareNotes once built (eg, technology maintenance and security and care coach compensation), it is likely that these costs are lower than other types of interventions. In addition, a mobile telehealth intervention like Brain CareNotes can remove some barriers to care partners (eg, geography) accessing BPSD support.

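### Reminding participants of the registry link a month before the final self-reported outcomes works against withholding the arm roles, and the claim of equal expectancy needs qualifying

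*Protocol article*

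**What the plan says.** All places are in the protocol article.

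- **Randomization:** "Participants will not be informed which app is the intervention and which is the control". Staff who collect primary and secondary outcomes at 6 and 12 months are masked.
- **Results:** trial results will appear on the public registry page, and "participants will be reminded of that link 1 month before their completion of the study". Analysis begins only when the last participant has finished, estimated for spring 2026. Publication is expected in late 2026 or early 2027.
- **Study Design; Assessments and Outcomes:** participation lasts 12 months, the last assessment is at 12 months, and both primary outcomes come from the Neuropsychiatric Inventory (NPI) as reported by the care partner.
- **Description of the Attention Control App:** "We will use an attention control comparator to mimic" technology use and access, then "frequency and type of contact with research staff (ie, for installation and technical support), and expectancy of benefit". The control app "provides education only, with no interactive BPSD management support, coaching, assessment, or external response".
- **Intervention Description (features textbox):** "each care partner user is assigned to a personal care coach employed by the study team". Coaches exchange messages with users and "schedule and conduct biweekly or monthly phone calls with the care partner".
- **Limitations and Potential Challenges:** the team is "sending app use reminders to participants in both the intervention and control groups every 2 weeks". Neither participants learning the arm roles nor unequal expectancy is listed as a limitation.

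**The concern.** Participants know which app they use. What the plan withholds is that app's role in the trial. Pointing every participant to a public description of the trial shortly before the primary endpoint works against that measure.

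The timing matters because the participant supplies the ratings. A care partner who believes they have the tested app may rate distress and symptoms more favourably, and one who believes they have the comparator may do the opposite. A masked interviewer removes rater bias but not this.

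The same mechanism bears on the claim that the comparator mimics expectancy. One arm has a named coach, two-way messaging and scheduled calls. The other has an education-only app that anyone can download. Expectations may differ between the arms even if no one reads the registry page.

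**Working it through.** The plan states no figure on this point. The check compares its sections, with one illustration of scale.

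**1. Timing of the reminder.** Follow-up is 12 months and the last assessment is at 12 months. The reminder comes 1 month before completion: 12 − 1 = month 11, before the 12-month NPI. This takes completion to coincide with the 12-month assessment, as the Study Design section implies.

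**2. What the reminder can offer at that time.** Its stated purpose is access to results. Analysis starts after the last participant completes, so at month 11 no participant, including the last, can find analysed results on the page. Sending the link after the final assessment loses nothing.

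**3. Who may still be affected.** By March 2025, 159 were enrolled and 42 had completed: 159 − 42 = 117. This is an upper limit for those enrolled by then, because withdrawals are not reported and some of the 117 may already have passed month 11.

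**4. What is matched between arms.**

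| Element | Brain CareNotes | Control |
|---|---|---|
| Help with app set-up and technical problems | yes | yes |
| Two-weekly reminders | yes | yes |
| Personal coach, messaging | yes | no |
| Scheduled coach calls over 12 months | about 12 (monthly) to 52/2 = 26 (biweekly) | 0 |

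The qualifier in the control-app section limits the staff-contact claim to the first row. It does not limit the expectancy claim, which stands unqualified. The call counts are the intended dose of the intervention, not an estimate of bias.

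**5. Scale, under assumed shifts.** Suppose there is no true effect but reporting differs between arms by b SD, with n per arm. A two-sided 5% z-test then rejects with probability

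Φ(b/√(2/n) − 1.96) + Φ(−b/√(2/n) − 1.96).

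With 75% of 80 retained, n = 60 and √(2/60) = 0.1826. For b = 0.2: 0.2/0.1826 = 1.095, so Φ(−0.865) + Φ(−3.055) = 0.194 + 0.001 = 0.195.

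| Assumed shift b (SD) | n = 60 per arm | n = 64 per arm |
|---|---|---|
| 0 | 0.050 | 0.050 |
| 0.1 | 0.085 | 0.087 |
| 0.2 | 0.195 | 0.205 |
| 0.3 | 0.376 | 0.396 |

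The documents give no value for b. The table shows only that a modest shift would matter in a trial of this size.

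**The case against.** Several counter-arguments have force.

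- **The registry page is not in the documents.** That it identifies the arms is an assumption. This stands, and the point is conditional on it.
- **Exposure did not begin at month 11.** A reminder implies that the link was given earlier, and the Setting and Participants section names the registry listing among the places where potential participants may find the study. Moving the reminder therefore cannot remove all exposure. This also stands. An active prompt just before the endpoint is still an addition that the trial can avoid.
- **Both arms get the reminder, and the 6-month NPI precedes it.** Equal delivery does not cancel the effect, because what is learned differs by arm. The 6-month data enter the mixed model, but the 12-month analysis of covariance uses the later, exposed measurement as its outcome.
- **Full participant blinding is not promised.** Correct. The text promises only that the roles are not disclosed, and claims masking for outcome assessors and analysts. The reminder conflicts with that narrower measure.

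A reader might go further and infer that attention matching was promised and not delivered, because only one arm has coach calls. The text does not support this. Contact matching is worded to cover app set-up and technical help only, so the calls do not breach it. Coaching is openly part of the intervention in the Abstract and the Intervention Description. Nor is it a fault that the trial cannot separate app from coach: the app-plus-coach versus education-only contrast is already stated, and the Limitations and Conclusions sections acknowledge coach cost and coach support.

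**Conclusion.** The concern holds in a limited form. The plan withholds the arm roles and then directs every participant to the public trial record about one month before the final self-reported primary outcomes. No results will exist at that time to justify the prompt. The harm depends on the page identifying the arms and on some participants reading it. Its size cannot be derived from the documents, and the false-positive rates above are illustrations under assumed shifts.

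Separately, equal expectancy of benefit cannot be assumed when only one arm has a personal coach, and the article neither qualifies that claim nor lists it as a limitation. This bears on how the self-reported outcomes are interpreted. It does not invalidate the comparison.

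**What to change.** 1. Send the registry reminder only after each participant's 12-month assessment is complete. The cost is one changed contact date and approval of the modification by the institutional review board, which the article requires before implementation. Access to results is not reduced.

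2. In the control-app section, say that contact is matched for app set-up, technical help and reminders, that total attention is not matched, and that equal expectancy is an aim that cannot be assumed.

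3. Add a limitation: participants may infer or learn the role of their app, the primary outcomes are self-reported, and assessor masking does not remove that source of bias. Items 2 and 3 cost a few sentences and a somewhat more cautious interpretation.

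No change to the comparator or to the stated treatment contrast is needed. For participants who have already had the reminder, the limitation sentence is the only remedy.
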